## Abstract

**Background:**

Anodal transcranial direct current stimulation (tDCS) over the primary motor cortex and cerebellum is gaining prominence in the literature due to its potential to favor learning and motor performance. If administered during motor training, tDCS is capable of increasing the effect of training. Considering the motor impairment presented by children with Autism Spectrum Disorders (ASD), atDCS applied during motor training may contribute to the rehabilitation of these children. However, it is necessary to examine and compare the effects of atDCS over the motor cortex and the cerebellum on the motor skills of children with ASD. This information may benefit future clinical indications of tDCS for rehabilitation of children with ASD. The aim of the proposed study is to determine whether anodal tDCS over the primary motor cortex and cerebellum can enhance the effects of gait training and postural control on motor skills, mobility, functional balance, cortical excitability, cognitive aspects and behavioral aspects in children with ASD. Our hypothesis is the active tDCS combined with motor training will enhance the performance of the participants in comparison to sham tDCS.

**Methods and design:**

A randomized, sham-controlled, double-blind clinical trial will be conducted involving 30 children with ASD that will be recruited to receive ten sessions of sham or ten sessions of active anodal tDCS (1 mA, 20 min) over the primary motor cortex or cerebellun combined with motor training. The participants will be assessed before as well as one, four and eight weeks after the interventions. The primary outcome will be gross and fine motor skills. The secondary outcomes will be mobility, functional balance, motor cortical excitability, cognitive aspects and behavioral aspects.

**Discussion:**

Although abnormalities in gait and balance are not primary characteristics of ASD, such abnormalities compromise independence and global functioning during the execution of routine activities of childhood. If demonstrated that anodal tDCS administered over areas of the brain involved in motor control, such as the primary motor cortex and cerebellum, can enhance the effects of gait and balance training in only ten sessions in two consecutive weeks, the clinical applicability of this stimulation modality will be expanded as well as more scientifically founded.

**Clinical trial registration** February 16, 2023 (https://ensaiosclinicos.gov.br/rg/RBR-3bskhwf).

## Introduction

1.

Autism spectrum disorder (ASD) is a neurodevelopmental condition with varied manifestations in terms of behavioral characteristics and adaptive functioning (1, 2). Although behavioral abnormalities are the main characteristics of the disorder, the number of children with ASD who seek motor rehabilitation has been increasing due to the negative impact that problems in motor control have on the daily living of this population (3–5). Approximately 83% of children with ASD have difficulties with their motor skills, with changes observed in gross and fine motor activities (5, 6). Furthermore, studies indicated delays in the acquisition of motor marks and fundamental motor skills (7, 8) as well as deficits in postural stability, an altered gait pattern, motor coordination problems and altered movement velocity (9–12).

The involvement of dysfunctional patterns of brain and cerebellum activity is increasingly clear with regards to abnormalities in the motor control of children with ASD. Some studies have demonstrated imbalances between excitation and inhibition in synaptic transmissions (13–15), with the involvement of frontostriatal circuits and cerebellar regions, which play an important role in the processing of information from the vestibular system and the control of balance (16–20). Although the dysfunctional patterns of the structures affect body stability and stability of the head during movement and global mobility, these structures also participate in cognitive functions and communication. An example is the participation of cerebellar processing in proprioception and fine motor control as well as attention, decision making, language and affective regulation (21, 22).

Children with ASD have abnormalities related to learning in the acquisition, retention and transference of motor skills (5), which are directly related to neurological controls of movement. The reduction in the activation of neural circuits necessary for the execution of gross and fine motor activities can be considered as one of the factors that can compromise the result of rehabilitation of children with neurodevelopmental disorders (23). Neurofunctional training requires the active practice of deficient motor activities, so that the execution of the necessary movements to perform the trained activity has an impact on increased brain activation. However, promoting increased activation of dysfunctional brain areas remained a major challenge for physical rehabilitation for a long time. Currently, rehabilitation has an important therapeutic tool, which, when associated with neurofunctional motor training, is capable of optimizing training results (24).

Noninvasive brain stimulation, specifically transcranial direct current stimulation (tDCS), has attracted increasing attention in the scientific literature on therapeutic interventions for individuals with ASD (25–28). Transcranial direct current stimulation is known to induce lasting changes in cortical excitability and is a safe, accessible form of noninvasive brain stimulation that involves the administration of a low-intensity monophasic electrical current to the scalp using sponge-silicone surface electrodes moistened with saline solution (29, 30). Cortical modulation is dependent on the polarity of the current. Anodal stimulation increases cortical excitability, favoring the depolarization of the neuronal membrane, whereas cathodal stimulation exerts an inhibitory effect through hyperpolarization of the neuronal membrane (31, 32). tDCS provides a modulatory effect on cortical function, being easy to apply and at a lower cost when compared to other transcranial stimulation techniques (33). The benefits of tDCS include the possibility of use during the execution of different activities and motor tasks and combining it with other interventions (34, 35).

Considering its potential to favor learning and motor performance, the administration of anodal tDCS over the primary motor cortex and cerebellum has been gaining prominence in the literature (33, 34, 36). The development of gait and balance is linked to brain development, with the motor cortex and cerebellum considered fundamental structures (37, 38). The primary motor cortex is related to specific aspects of movement, such as direction, speed, acceleration and strength (39, 40). Anodal tDCS over this area of the brain has been performed in numerous studies involving individuals in all cycles of life, demonstrating that the promotion of the cortical modulation of neural networks has the potential to alter and favor learning and the consolidation of motor patterns, especially if stimulation occurs in synchrony with motor training (41, 42). Likewise, anodal tDCS over the cerebellum can result in faster, more effective adaptations in terms of locomotion and postural control. Anodal cerebellar stimulation is believed to facilitate the connectivity between the cerebellum and motor cortex through cerebellar-thalamocortical pathways (43, 44). Thus, the administration of electrical current could benefit motor control through direct and indirect effects in areas of the brain responsible for the control of body movements, short-term memory and postural control.

In the last decade, clinical trials have begun to demonstrate the promising effects of tDCS in the physical rehabilitation of children with motor impairments (45–50). Considering the pediatric population, children with cerebral palsy represent the most frequently studied population in studies on transcranial stimulation. These studies have shown that anodal tDCS over the motor cortex can manage effects on movement control, functional mobility, gait, gross motor function and balance (45, 46, 48–50). Likewise, the clinical trial analyzing the effects of anodal cerebellar tDCS demonstrated better effect on the spatio-temporal gait parameters and static balance of children with ataxic cerebral palsy (47). The effects were mainly observed when tDCS was applied during ten sessions (20 min) of motor training (51). The results on motor activities are directly related to the type of motor training, for example, if gait is trained during the application of anodic tDCS, the main results observed will be on gait and mobility (24). The target brain areas of transcranial stimulation that promoted positive effects on motor skills were the primary motor cortex, the area most frequently studied in children with motor disorders, and the cerebellum (51). Furthermore, predictive factors of positive tDCS responses were identified, the main ones being the presence of the motor evoked potential in the pre-intervention evaluation and subcortical encephalic lesions (24).

Recent evidence has demonstrated the promising results of tDCS for individuals with ASD, with a reduction in the intensity of the symptoms of the disorder, especially with regards to communication (nonverbal and social), a reduction in stereotyped movements and an improvement in working memory (28, 52, 53). However, clinical trials involving children with ASD have almost exclusively analyzed the effects of anodal tDCS over the left dorsolateral prefrontal cortex (54–57) or the temporoparietal junction with the aim of affecting dysfunctional areas directly related to the primary diagnostic characteristics of the disorder (compromised executive functions and social communication) (58). The effects of tDCS over the primary motor cortex during motor training were the focus of only one clinical trial identified to date, which reported promising results in terms of balance and motor skills in children with ASD (59). One study analyzed the effects of ten sessions of bilateral cerebellar anodal tDCS on the electroencephalographic activity of children with ASD. The results demonstrated that the active tDCS presented better results than those obtained with the placebo stimulation in the modulation and in the increase of the cerebral complexity. Increased complexity was observed in the cerebellar-cerebral circuitry, mainly in the left and right frontal cortical regions, the right central cortical region, and left parietal cortical region (60). However, this clinical trial exclusively analyzed the effects of tDCS on the motor cortex, and no studies were identified in the literature that analyzed the effects of tDCS on the cerebellum – the brain area that is related to the poor balance control shown by children with ASD.

As a resource considered safe, inexpensive and easy to administer, tDCS could contribute to the rehabilitation of these children, as its neurophysiological effects have been demonstrated to favor the learning of new voluntary motor and postural control strategies. Considering the complexity of brain activity dysfunctions observed in ASD, we need to investigate whether anodal tDCS may (or may not) contribute to motor training results. In addition, it is necessary to understand what are the effects of facilitating cortical excitability of fundamental structures of motor control, such as, for example, the primary motor cortex and the cerebellum. This information may benefit future clinical indications of tDCS for rehabilitation of children with ASD. However, the scientific literature is extremely limited regarding the effects of tDCS on areas of motor control in children with ASD.

The main goal of the present study is to compare the effects of ten 20-min sessions of neurofunctional motor training combined with anodal tDCS over the primary motor cortex, cerebellar region and sham stimulation on motor ability in children with ASD. Specifically, the aim is to determine whether anodal tDCS over these areas of the brain can optimize the effects of gait and postural control training on gross and fine motor skills, mobility, functional balance, motor cortical excitability, cognitive aspects and behavioral aspects in children with ASD. Our central hypothesis is that all individuals will present functional improvements following gait and balance training, but the benefits will be more evident after the administration of active tDCS (primary motor cortex and cerebellar region) compared to the group receiving sham tDCS due to the neurophysiological effects on cortical excitability. Moreover, we believe that the effects of anodal tDCS over the primary motor cortex will be restricted to motor outcomes, whereas the effects of anodal stimulation over the cerebellar region will also be found in outcomes related to cognitive and behavioral aspects.

## Methods

2.

We Registered this trial on The Brazilian Registry of Clinical Trials (RBR-3bskhwf). This paper has been reported in accordance with the standard Protocol Items: Recommendations for Interventional Trials (Spirit) (61). The study was reviewed and approved by Ethical Committee of the Evangelic University of Goias, under the number CAAE: 64474922.0.0000.5076. Written informed consent to participate in this study was provided by the participants’ legal guardian/next of kin.

### General study design

2.1.

A randomized, sham-controlled, double-blind study will be conducted involving children with a diagnosis of ASD. We will compare three montages: anodal tDCS over the primary motor cortex, anodal tDCS over the cerebellar region and sham stimulation. Stimulation will be administered in all three groups during 20 min of motor training focused on gait and balance training (Figure 1).

**Figure 1 fig1:**
[figure not shown]
List of specific time points on this line. Motor training associated with tDCS (active or sham) at a frequency of five sessions per week for two consecutive weeks (total of ten sessions). MABC-2, Movement Assessment Battery for Children-2; PBS, Pediatric Balance Scale. TUG, Timed Up and Go; ADOS, Autism Diagnostic Observation Schedule; CARS, Childhood Autism Rating Scale.

The study will involve the following visits:

Visit 1: Screening of participants according to the eligibility criteria and signing of the statements of consent.Visits 2 and 3: Initial assessment (pre-intervention) one week prior to the onset of the intervention, with the investigation of motor ability, mobility, functional balance, motor cortical excitability, cognitive aspects and behavioral aspects. After the initial assessment, the participants will be randomly allocated to the different intervention groups. These visits will be held on two non-consecutive days and will last a maximum of 1.5 h.Visits 4 to 14: Ten intervention sessions in accordance with the allocation to the different groups. Sessions will be held for two consecutive weeks at a frequency of five sessions per week (Monday to Friday) with a maximum duration of approximately 45 min, 20 min of which will be tDCS combined with motor training.Visits 15 and 16: Post-intervention assessment one week after the end of the intervention with the investigation of motor ability, mobility, functional balance and motor cortical excitability. These visits will be held on two non-consecutive days and will last a maximum of 1.5 h.Visits 17 and 18: First follow-up assessment four weeks after the end of the intervention, with the investigation of motor ability, mobility, functional balance, motor cortical excitability, cognitive aspects and behavioral aspects. These visits will be held on two non-consecutive days and will last a maximum of 1.5 h.Visits 19 and 20: Second follow-up assessment eight weeks after the end of the intervention, with the investigation of motor ability, mobility, functional balance, motor cortical excitability, cognitive aspects and behavioral aspects. These visits will be held on two non-consecutive days and will last a maximum of 1.5 h

Figure 2 displays the flowchart of the study in accordance with the SPIRIT statement (61).

**Figure 2 fig2:**
[figure not shown]
SPIRIT: Description of protocol of study, timeframe of enrolment, interventions and assessments. MABC-2, Movement Assessment Battery for Children-2; TUG, Timed Up and Go. PBS: Pediatric Balance Scale; MEP, Motor Evoked Potential; ADOS, Autism Diagnostic Observation Schedule; CARS, Childhood Autism Rating Scale.

### Participants

2.2.

Thirty children will be recruited from the XXX Child Neurorehabilitation Clinic in the city of XXX, XXX. Participants will undergo detailed screening with the eligibility criteria for inclusion in the study.

The sample size was calculated considering the primary clinical results, which are the total and balance score of the Movement Assessment Battery for Children, 2nd ed. (MABC-2) (62). The calculation of the sample size was based on data from a study involving a group of individuals with ASD who received motor training combined with tDCS over the primary motor cortex (59). The estimated effect size of the previous study was 1.39 (change in total MABC-2 score of 16.5 with a standard deviation [SD] of 5.98; change in score of balance category of MABC-2 of 2.4, SD: 1.70; α = 0.05 (two-tailed) and β = 0.8). The estimate indicated a minimum of 24 participants (eight per group). Considering a possible dropout rate of 20%, 30 participants will be recruited.

The children will be screened for participation in the study based on the following:

Inclusion criteria: 1) Diagnosis of ASD confirmed though a clinical examination; 2) Standard neurobehavioral assessment that confirms and categorizes the severity of ASD; 3) Levels I, II and III according to the Diagnostic and Statistical Manual of intellectual disability (DSM-5); 4) Age three to eight years; 5) Sufficient response to understand simple verbal commands; 6) No change in medication in the six months prior to the onset of the study or during the study; 7) Signed statement of informed consent by a legal guardian; 8) Agreement to participate in study through term of assent.

Exclusion criteria: 1) Diagnosis of epilepsy or seizure within the 12 months prior to the onset of the study; 2) Neurological, neuromuscular disorders or syndromes other than ASD; 3) Having been submitted to orthopedic or neurological surgery within 12 months prior to the intervention; 4) Orthopedic deformities with indication for surgery; 5) Implants in the skull or having undergone some neurosurgical procedure; 6) Metallic implants in the head, neck, chest or upper limb; 7) Hearing devices; 8) Degree of cooperation incompatible with the adequate performance of the activities proposed in the present project.

Withdrawal criteria: Participants who decline to continue in the study, those not present on the days of the experiment and those who miss up to two of the 10 intervention sessions will be removed from the study.

**Randomization procedure:** Randomization will be performed using a program for the generation of random numbers to allocate the participants to one of the following interventions:Experimental group 1 – Motor cortex stimulation: anodal tDCS over the primary motor cortex combined with neurofunctional motor training;Experimental group 2 – Cerebellar stimulation: anodal tDCS over the cerebellar region combined with neurofunctional motor training;Control group – Sham stimulation: sham tDCS combined with neurofunctional motor training.

Randomization will be performed considering stratification based on the severity of ASD according to the Brazilian version of the Childhood Autism Rating Scale (CARS-BR) (63). The randomization sequence will be generated for each category (mild, moderate and severe) with adequately organized distribution in sequentially numbered opaque envelopes.

**Blinding:** After the inclusion of participants based on the eligibility criteria and after the pre-intervention assessment, the allocation of the participants will be informed to the researcher who will carry out the intervention. The researcher in charge of the randomization process will not participate in any other aspect of the study and will not have access to the participants. The researchers involved in the assessment procedures, the participants and their families will not be aware of the allocation of the participants. This information will be provided to the families and participants after the complete conclusion of the procedures of the study. The investigator in charge of the interventions will not be blinded to the allocation of the participants, as it will be necessary to select the active or sham stimulation option of the equipment.

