##### Primary outcome

2.3.2.1.

Gross and fine motor skills: Motor skills will be assessed using the Movement Assessment Battery for Children-2 (MABC-2). The principal aim for the use of this measure will be the assessment of balance using a valid measure for children with ASD (69, 70) employed in a previous clinical trial analyzing the effects of tDCS in this population (59). The MABC-2 comprises the categories of manual dexterity, aiming and catching and balance, with norms of the tests for three different age groups (3–6 years, 7–11 years and 12–17 years). The balance subscale has three items for each age group (one static and two dynamic tests). The standard score based on age is equivalent in percentile for each subscale to be transcribed from the raw score of the child. The percentiles are normally used to guide the interpretation when explaining the scores obtained on the test to parents and teachers, with the following zones: (a) Red zone – scores equal to or lower than the 5th percentile; (b) Amber zone – scores between the 5th and 15th percentile; and (c) Green zone – scores above the 15th percentile (69–71).

The MABC is used to identify motor difficulties in children and is particularly associated with the identification of Developmental Coordination Disorder (DCD). The assessment has been used and validated with several atypical populations, including those with ASD. Since there is no recommendation or guideline for evaluation of motor ability in individuals with ASD, the MABC was an optimal choice for the present study. Several studies have shown that individuals with ASD have motor difficulties consistent with DCD. In Miller et al. (72), over 90% of the cases in the ASD group met criteria for co-occurring DCD. In a recent systematic review, the majority of articles (92.5%) indicated that 50–88% of children with ASD had significant motor impairments on standardized motor assessments and/or functional questionnaires. The nature of motor and function problems in ASD were consistent with DCD (6).

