Neurofunctional training: The training was carried out in a therapy room organized specifically for the intervention. Composed of postural control training and gait training. Immediately after the onset of tDCS (active or sham), the three groups will perform neurofunctional training consisting of postural control exercises and treadmill training conducted by a trained, experienced physiotherapist, with the participants performing the intervention individually. The 20 min of intervention will be divided into two steps (10 min each).Treadmill training: The training was performed on a Inbramed treadmill (Milenium ATL model, RS, Brazil). The treadmill training speed will be established based on the performance of the child in each session. Ideal speed will be the maximum speed at which the child is able to walk with adequate support of the feet upon initial contact and throughout the entire support phase of the gait cycle. The speed will be gradually increased during the initial two minutes and gradually reduced during the final two minutes, maintaining a constant speed in the interim. During training, the children used their habitual shoes, which were duly placed by the physiotherapist. The therapist remained behind the participants, facilitating gait training if necessary and ensuring both the safety of the intervention and the best possible movement kinematics. Throughout treadmill training, the therapist in charge also provided verbal commands to the participant to improve the execution of gait (48, 78).Postural control exercises: The second step will involve a circuit of activities based on the tasks of the MABC-2 to favor the improvement in postural control. The activities will be four exercises performed for 40 s with a 20-s rest interval. The four exercises will be selected individually according to the performance of each child during the MABC-2. Items from the balance and aim subscale will be defined as circuit exercises, which the child is able to perform with a delay (does not reach the complete performance of the item) and with qualitative observations in aspects of posture/body control. Some examples of activities are: balancing on one foot, walking on tiptoes, jumping, etc. During the execution of the circuit activities, the physiotherapist will remain beside the child, guaranteeing his/her safety in the face of imbalance and offering verbal commands with motivational phrases and guidance for the steps of the activities. Each participant will perform two complete circuits, with a two-minute rest interval between circuits.

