
### Statistical analysis

2.5.

The precision of all data will be verified by two researchers and a blinded statistician will conduct all analyses. The Kolmogorov–Smirnov test will be used to determine the distribution of the data regarding adherence to the Gaussian curve. Parametric data will be expressed as mean and standard deviation or 95% confidence interval. Nonparametric data will be expressed as median and interquartile range. Two-way analysis of variance (ANOVA) followed Tukey’s *post hoc* test will be used to assess the effects of tDCS on the outcome variables. For all analyses, the fixed independent variables will be group (active tDCS over the primary motor cortex, active tDCS over the cerebellum and sham tDCS) and assessment time (pre-intervention, post-intervention, follow-up 1 and follow-up 2). The dependent variables will be the outcomes studied. The effect size (Cohen’s d) will be calculated from the difference in the values obtained during the pre-intervention, post-intervention, first follow-up and second follow-up assessments comparing the three groups. Predictive response factors will be identified through logistic regression analysis. Logistic regression models will be performed with the outcomes: type of daily medication, ASD severity, MEP (presence or absence) and pre-intervention MABC-2 result. The level of significance will be set at 5% (*p* < 0.05) and Statistical Package for the Social Sciences (SPSS, version 21.0) will be used for the analyses.

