## Discussion

3.

Motor training combined with tDCS has been shown to be safe, viable and effective for children and adolescents with motor control disorders. Considering the results available in the scientific literature demonstrating the promising effects of anodal tDCS in children with ASD, especially aspects related to communication and behavior, it is of interest to expand the knowledge regarding the effects of tDCS also on motor skills in this population. If demonstrated that anodal tDCS administered over areas of the brain involved in motor control, such as the primary motor cortex and cerebellum, can enhance the effects of gait and balance training in only ten sessions in two consecutive weeks, the clinical applicability of this stimulation modality will be expanded as well as more scientifically founded.

Although abnormalities in gait and balance are not primary characteristics of ASD, such abnormalities compromise independence and global functioning during the execution of routine activities of childhood. Motor rehabilitation poses a challenge for therapists, families and patients, as children with ASD are often enrolled in behavioral treatment programs that require a considerable number of intervention hours per day. Thus, therapeutic possibilities with execution in focused, short-term programs that prove effective could be a favorable option for the treatment of abnormalities in motor skills.

Therefore, the present protocol for a randomized controlled clinical trial involves assessment measures of results with representativeness in the daily activities of children. Motor skills will be assessed using the MABC-2, which consists of items that measure gross and fine motor skills, to determine whether motor training (gait and balance) combined with anodal tDCS achieves positive results not restricted to the motor task being trained. Scales and tests will be used to measure the effects on mobility and balance during functional activities, such as walking, standing up, sitting down, changing direction, etc. These assessment tools will enable the understanding of the effects on an important domain of the International Classification of Functioning, Disability and Health – ACTIVITY, which is the primary focus of the proposed intervention.

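### Two MABC-2 scores are named as primary with no rule linking them, so if either may carry the trial the primary false-positive rate is about 7.5 to 10%, not 5%

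*Protocol article*

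**What the plan says.** The article describes the primary outcome in several places.

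- Abstract, Methods and design: "The primary outcome will be gross and fine motor skills". Sections 2.3 and 2.3.2.1 say the same and name the MABC-2 as the instrument.
- Section 2.2 (sample size) becomes specific and names two scores: "the primary clinical results, which are the total and balance score of the Movement Assessment Battery for Children".
- Section 2.3.2.1 then singles out one of them: "The principal aim for the use of this measure will be the assessment of balance".

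Section 2.5 plans, for each outcome, a two-way ANOVA with group (three levels) and assessment time (four levels) as factors, followed by Tukey's test. On the error rate it says only "The level of significance will be set at 5" percent. It gives no either/both rule for the two scores, no division of the 5% and no order of testing.

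Two further statements bear on interpretation. In section 2.4, on the postural control circuit: "Items from the balance and aim subscale will be defined as circuit exercises". In the Discussion, the MABC-2 is meant to show whether the combined treatment "achieves positive results not restricted to the motor task being trained".

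**The concern.** With two primary scores, each analysed at 5%, the chance of at least one false-positive primary result depends on the success rule, and the article states none. If a significant result on either score counts, the rate is above 5%. If both are needed, it is not. Tukey's procedure does not settle this, because its family is the set of comparisons inside one score's ANOVA.

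With about ten children per arm, the report could present whichever score turned out significant as the primary finding, and the article would give the reader no basis for objecting.

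There is also a smaller matter of interpretation. The circuit drills items from two of the three MABC-2 components. A gain on balance or on the total could then be reported as transfer when it reflects, at least in part, what was practised.

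**Working it through.** **Inputs from section 2.2.** Total score: change 16.5, SD 5.98. Balance score: change 2.4, SD 1.70. Stated effect size 1.39. "α = 0.05 (two-tailed) and β = 0.8", where the 0.8 is evidently power. Minimum 24 (eight per group); 30 after 20% dropout.

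**Step 1: which score does the sizing use?** Balance: 2.4/1.70 = 1.41. Total: 16.5/5.98 = 2.76. The stated 1.39 is close to balance and about half the total.

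Normal formula for one two-group comparison, n per group = 2(1.960 + 0.842)²/d²:

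- d = 1.41: 7.88, so 8 per group and 24 in all.
- d = 1.39: 8.12, which is 8 only if rounded to the nearest whole number.
- d = 2.76: 2.06, so 3 per group.

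24/0.8 = 30. The published 24/30 is therefore reproduced from balance and not from total.

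**Step 2: error rate with two scores at 5%.** If the scores were independent: 1 − 0.95² = 9.75%. Upper limit whatever the correlation: 2 × 5% = 10%.

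The article gives no between-score correlation, so a range is assumed. Null trials were simulated (20,000 runs per setting; three groups of 8 or 10; four times; within-child correlation 0.5 or 0.8; time handled as a repeated measure). Ranges are across the group sizes and within-child correlations.

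| Between-score correlation (assumed) | Interaction significant on either score | Tukey at one time, either score | Interaction significant on both scores |
|---|---|---|---|
| 0 | 9.5–10.1% | 9.6–10.0% | 0.2–0.3% |
| 0.5 | 9.0–9.3% | 9.1–9.3% | 0.7–0.8% |
| 0.7 | 8.3–8.6% | 8.6–9.0% | 1.2–1.5% |
| 0.9 | 7.4–7.5% | 7.0–7.3% | 2.7–2.8% |

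The same interaction test on one score gave 4.8–5.3%, so the excess comes from having two scores. The last column assumes no effect on either score.

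**Step 3: cost of keeping both scores as alternatives.** Holm's first step across two scores uses 0.025. The normal formula becomes 2(2.241 + 0.842)²/d²: 9.54 for d = 1.41 and 9.84 for d = 1.39, so 10 per group. That is 30 before dropout and 30/0.8 = 37.5, so 38 after (39 for equal groups). With the t distribution it is 11 to 12 per group: 33 to 36 before dropout and 42 to 45 after. With eight per group, t-based power falls from 73–75% at 0.05 to 61–63% at 0.025.

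**Step 4: trained versus untrained content.** Section 2.3.2.1 lists three MABC-2 components: manual dexterity, aiming and catching, and balance. Section 2.4 draws the circuit from balance and aiming items. Only manual dexterity lies outside the circuit.

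**The case against.** Much of the apparent disagreement is one of level. The abstract and sections 2.3 and 2.3.2.1 name a construct and an instrument, section 2.2 names scores, and the sentence about balance partly explains why the instrument was chosen. This stands: the instrument is the same throughout, and the real ambiguity is total versus balance.

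A separate analysis plan, not shown, could hold a testing order. That is fair for the decisive time and contrasts, which are often left to such a document. It is weaker for the two scores, because the article itself names both as primary and sets a flat 5%.

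A reader might go further, count two scores by two active-versus-sham contrasts by three post-treatment times, treat them as twelve separate tests at 5%, and infer an error rate several times the nominal one. The article does not support that. Section 2.5 makes time a factor in one ANOVA per score and follows it with Tukey's test. Separate testing at each time is not prescribed. The times are not presented as interchangeable either: one week is labelled post-intervention, weeks four and eight are follow-up, and section 2.9 speaks of effects being maintained.

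A reader might also infer that drilling test items biases the comparison with sham. It does not by itself, since all three groups do the same training. Nor is the total wholly practised content: it includes manual dexterity, and only four individually chosen items are drilled. What remains is a limit on what a gain in balance or total can be said to show.

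**Conclusion.** The point holds for the two primary scores. If significance on either score is enough, the primary false-positive rate is about 7.5 to 10%. The lower end rests on an assumed between-score correlation of 0.9 and the upper end on none. Since the total contains balance, a positive correlation is likely and the upper end less so. If both scores must be significant, the rate stays below 5%. The figures assume one decisive test per score and an analysis that respects the repeated measurements. They say nothing about secondary outcomes.

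The transfer issue is separate and minor. It affects the wording of a conclusion, not the validity of active versus sham.

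**What to change.** Before unblinding, do one of the following.

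1. Name one primary score and make the other secondary. This is the simplest. Balance fits the article best: it matches the effect size of 1.39, it reproduces 24/30 on the plan's own formula, and section 2.3.2.1 gives it as the principal aim.
2. State that both scores must be significant. No division of the 5% is needed, but power for the joint requirement should be given.
3. Keep both as alternatives with Holm across the two, and restate the power or sample size as in step 3 of the working.

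In each case, name the one-week post-intervention assessment and the two active-versus-sham contrasts as decisive, and make weeks four and eight secondary tests of maintenance. Align the abstract and sections 2.2, 2.3.2.1 and 2.5 with the choice.

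Separately, rest any claim of effects beyond the trained task on the manual dexterity component.

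Cost: wording only for option 1; the other score and the later times lose primary status. Option 2 costs power. Option 3 costs power or more children.
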